### Provisions for post-trial care {30}

There are no provisions for participant management after completion of the study. Any ongoing management relating to HCV infection will be at the discretion of the participant’s nominated care provider.

### Outcomes {12}

#### Primary endpoint

Initiation of DAA therapy for HCV within 12 weeks of registration, as evidenced by the valid dispensed DAA medication.

#### Secondary endpoints

Evidence of having had a HCV PCR test (regardless of result) within 12 weeks (84 days) of registrationNumber of scheduled/recommended days in which DAA therapy was not taken, irrespective of the prescribed duration of therapy (i.e. 8 weeks or 12 weeks):◦ < 7 days,◦ 7–13 days,◦ 14–20 days,◦ 21–27 days,◦ 28 + days,as self-reported (via SMS or to the navigator) at approximately 28 days after the expected end date of therapy (DAA therapy usually has a duration of 2–3 months).Sustained virological response (SVR), defined as a negative HCV RNA PCR test at any time from at least 4 weeks (28 days) after completion of DAA therapy and before 12 months after registration.

### Participant timeline {13}

The main steps in the participant timeline are (see Table 1):

**Table 1 Tab1:** Study-related events and the associated participant timeline

Events	Time point	Data collected	Type of contact
Registration and randomisation	On Registration – Time 0	Date of registration	SMS interface
Enrolment	As soon as practicable after registration, and not ≥ 12 weeks afterwards	Date of enrolment	Navigator phone/video call
PCR confirmation	As soon as practicable after enrolment, and not ≥ 12 weeks after registration	Evidence and date of HCV RNA PCR testing	Navigator phone/video call
Treatment initiation	As soon as practicable after PCR confirmation, and not ≥ 12 weeks after Registration	Evidence and date of dispensed DAA medication (**Primary outcome**)	Navigator phone/video call
Mid-treatment check-in	14 to 27 days after treatment initiation	Any adverse events (any untoward health-related events)	Navigator phone/video call
End-of-treatment check-in	4–5 weeks after scheduled treatment completion	Participant’s adherence to treatment (number of missed dosages)	SMS-based survey and/or Navigator phone/video call
SVR check	4 to 24 weeks after treatment completion	Evidence and date of SVR result	Navigator phone/video call

#### Registration

The SMS-based registration interface (underpinned by the Twilio platform—https://www.twilio.com), once initiated by the participant, prompts the user to respond to a series of self-assessed eligibility questions. Appropriate responses to all eligibility questions progress the potential participant through to successful registration, at which point they will be considered ‘registrants’ and will be informed of the randomly generated incentive amount they will be eligible for in return for providing evidence (within 12 weeks) of initiating DAA therapy. If the registrant confirms through the SMS registration interface that they wish to proceed with the project and are willing to be contacted by a treatment navigator, they are sent a link to the PIS on the project website and informed to expect contact from a treatment navigator within 72 h.

#### Enrolment (and consent)

The treatment navigator contacts (via telephone) all registrants who indicate their desire to be contacted. The navigator assesses and confirms the registrant’s eligibility for enrolment. After this, they explain the procedures, processes and data collection requirements of the project and clarify roles and responsibilities. The registrant becomes an ‘enrolled participant’ once they provide verbal consent (as detailed above) for participation in the study, and this date is defined as the date of enrolment.

#### Nomination of a preferred treatment prescriber

Following receipt of consent, participants are invited to nominate a primary care provider as their preferred DAA treatment prescriber. If the participant nominates a preferred prescriber, the navigator initiates the randomisation of the co-incentive payment for the prescriber via the navigator portal, another component of the MOTIVATE-C management system. The navigator then contacts (email, phone and/or fax) the participant’s preferred prescriber to provide a brief description of the project and to inform them that an un-named participant has nominated them as their preferred prescriber. If a co-incentive payment of AUD 100 has been assigned at randomisation, the preferred treatment prescriber will also be notified that they are eligible for a co-incentive payment on demonstration of treatment initiation by the participant.

If the participant does not nominate a preferred prescriber, or if their nominated prescriber indicates they are unwilling or unable to accept the participant, the navigator helps the participant to identify an alternative DAA treatment prescriber from a default list of experienced primary care HCV treatment providers. Default prescribers are not randomised to a co-incentive payment but are instead provided a compensation payment of AUD 50.

#### Evidence of HCV testing and dispensed DAA medication

At enrolment, the treatment navigator explains to the participant that it is expected that they will, as soon as practicable, make an appointment with the treatment prescriber (either face-to-face or via telehealth), receive a pathology referral to confirm active HCV infection by PCR (unless the prescriber deems it not necessary), and attend a pathology collection centre for confirmatory HCV testing. On receipt of the results of the confirmatory HCV PCR test(s), it is expected that the participant will inform the navigator (via video call or SMS) of the results (irrespective of whether positive or negative). Unless the HCV PCR test excludes active infection, the participant will need to obtain a prescription for DAA therapy from the prescriber, although the appropriateness of therapy and the decision to prescribe remains at the sole discretion of the prescriber in consultation with the participant; a prescriber also has the discretion to refer to a specialist prescriber if deemed clinically necessary. The participant is expected to fill the DAA prescription at any pharmacy.

Upon sighting (via video call or SMS) and validating the positive HCV test results and the dispensed DAA, the navigator initiates payment of the HCV test compensation (AUD 105) and the treatment incentive (if randomised to a non-zero amount) to the participant as either a digital or physical debit card. If applicable, a co-incentive payment for the nominated treatment prescriber (or compensation payment for a default prescriber) is also initiated as either a digital or physical debit card. If the HCV test results exclude active infection, the navigator initiates payment of the HCV test compensation (AUD 105) and documents the negative result on the navigator portal, and nothing further is required from the participant for the project. Where applicable, if the participant has not provided evidence of a filled DAA prescription within 4 weeks of testing, the navigator reminds the participant of the requirements to be eligible for an incentive payment.

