## Interventions

### Explanation for the choice of comparators {6b}

Currently, there is little understanding about what constitutes an effective incentive value in this patient population. In consultation with stakeholders including people with lived experience of HCV infection and with injecting drug use, we have set a range from AUD 0 to 1000 in increments of AUD 50. The upper bound for the incentive values was selected based on stakeholder feedback as the value above which one would expect little incremental gain in the propensity to commence DAA treatment. The lower bound of AUD 0 provides a proxy for the status quo, i.e. absence of a financial incentive. The estimated response on each incentive value will be compared to the reference value (AUD 0) to determine whether it constitutes a minimally effective dose. However, it must be noted that all participants, including those assigned AUD 0 incentive, will have access to the navigator support program and will be eligible for a compensatory payment for HCV testing (see below), so any effect of the interventions need to be interpreted within that context.

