**Enrolled participants only**		
Name	For participant identification and validation of evidence of testing/prescription/SVR	At the initial meeting with the navigator
Date of birth	To permit adequate description of the study population and validation of evidence of testing/prescription/SVR	
Sex		
Mailing address	Only if participant requests for a hardcopy of the PIS and/or physical gift card to be delivered	
Date of enrolment in the study, *i.e. the date that the participant provides verbal consent to the navigator*	To track compliance with project timelines	At the initial or follow-up meeting (if participant require more time) with the navigator
Date and results of the HCV test	Secondary endpoint and to trigger compensation payment and to track compliance with project timelines	At the navigator-participant meeting to demonstrate evidence of HCV test
Name of the nominated treatment prescriber (including name of the practice)	To enable provision of the compensation payment	At the navigator-participant meeting to demonstrate evidence of DAA prescription
Date of treatment initiation	Primary endpoint and to trigger incentive payment and to track compliance with project timelines	
Adverse events (any untoward health-related events including medical attendance or hospitalisation)	For safety monitoring	At the navigator-participant meeting 2–4 weeks following initiation of treatment
Self-reported number of scheduled/recommended doses of DAA not taken grouped into:	Secondary endpoint	28 days following completion of treatment
• < 7 days,		
• 7–13 days,		
• 14–20 days,		
• 21–27 days,		
• 28 + days		
Date and results of the SVR test	Secondary endpoint and to trigger final compensation payment	4–24 weeks following completion of treatment

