### Plans to promote participant retention and complete follow-up {18b}

The treatment navigators will foster a positive relationship with the participants by providing support, including facilitation of appointments if requested, sending reminders of timelines, clarifying any queries and helping to resolve issues that arise during the participant’s progression in the study. At each navigator-participant contact, the participant is informed/ reminded of the requirements for the next step of the study and the associated timeline. Following registration, at each expected, pre-determined point of contact, the treatment navigator attempts to contact the participant for a maximum of three attempts, at least 24 h apart over a 14-day window period.

Furthermore, regardless of any financial incentives offered, all participants are eligible to receive compensatory payments for testing to confirm HCV infection prior to initiation of DAA therapy (AUD 105), and to undergo a test of HCV viral clearance after completion of DAA therapy (AUD 75). Default prescribers, who are not randomised to a co-incentive, are eligible to receive a compensatory payment for each DAA prescription (AUD 50).

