### Limitations

In an ideal study, the proposed intervention, i.e. the offer of incentives of various values, would be compared against no incentive in the context of usual practice. At present in Australia, a number of community-based organisations offer peer-based treatment support and navigation, although this is not available universally. In MOTIVATE-C, incentives are offered in the context of a program of treatment support by trained navigators, and participants receive compensation for adhering to study-related procedures (for HCV testing before and after treatment) regardless of whether they are assigned to any incentive. Therefore, any observed effectiveness of incentives must be interpreted within this context. While the question of the effectiveness of incentives outside of a treatment support program and without compensation payments will remain unanswered, it was deemed important on ethical grounds that all participants are compensated for their time and that all stand to derive some benefit from participation, even if not assigned to an incentive [20].

In conclusion, we anticipate that the offer of financial incentives will be shown to be a straightforward, readily implementable, and cost-effective strategy for curing the 74,400 Australians still living with HCV [5], and thereby help Australia to achieve HCV elimination.

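### Read literally, the payment step makes the AUD 105 test compensation depend on dispensed DAA in PCR-positive participants, while the rest of the article ties it to testing

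*Protocol article*

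**What the plan says.** All places are in the protocol article.

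- **Evidence of HCV testing and dispensed DAA medication.** For a participant with a positive test, the navigator acts upon sighting and "validating the positive HCV test results and the dispensed DAA, the navigator initiates payment of the HCV test compensation (AUD 105", in the same step as the randomised incentive. For a negative test: "If the HCV test results exclude active infection, the navigator initiates payment of the HCV test compensation (AUD 105". The section has no step that pays a PCR-positive participant who does not start DAA.
- **Follow-up.** Receipt of the compensation, with or without an incentive, is confirmed 2 to 4 weeks after treatment initiation.
- **Table 2, enrolled participants.** The date and result of the HCV test serve as "Secondary endpoint and to trigger compensation payment and to track compliance with project timelines". The date of treatment initiation is a separate row: "Primary endpoint and to trigger incentive payment and to track compliance with project timelines".
- **Plans to promote participant retention {18b}.** "all participants are eligible to receive compensatory payments for testing to confirm HCV infection prior to initiation of DAA therapy (AUD 105".
- **Explanation for the choice of comparators {6b}.** AUD 0 "provides a proxy for the status quo, i.e. absence of a financial incentive". The same section adds that everyone, the AUD 0 arm included, "will be eligible for a compensatory payment for HCV testing (see below), so any effect of the interventions need to be interpreted within that context".
- **Limitations.** "participants receive compensation for adhering to study-related procedures (for HCV testing before and after treatment) regardless of whether they are assigned to any incentive".

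**The concern.** Dispensed DAA within 12 weeks of registration is the primary endpoint. A payment released only when the dispensed DAA is sighted is, for the person deciding whether to start, an incentive to start. If the literal step is followed, each arm offers a PCR-positive participant AUD 105 more for initiating than its label says.

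AUD 0 is the reference for the 10-point effectiveness criterion. The futility rule and the allocation weights are both built on the probability of meeting that criterion, and AUD 0 also stands for no incentive in the first research question. A shift of AUD 105 is 105/50 = 2.1 steps of the dose grid. The economic analysis would also price each arm at the wrong contingent amount.

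There is a second consequence. Having had a PCR test within 12 weeks, regardless of result, is a secondary endpoint. Under the literal step, PCR-positive participants who do not start DAA have no payment reason to show their test, whereas PCR-negative participants do. The endpoint may be under-recorded in the former.

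**Working it through.** **Text comparison**

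| Place | What releases the AUD 105 | Who |
|---|---|---|
| Evidence section, positive test | test and dispensed DAA, both sighted | PCR-positive |
| Evidence section, negative test | test alone | PCR-negative |
| Table 2 | test date and result; initiation listed separately, for the incentive | enrolled participants |
| Retention {18b} | testing | all participants |
| Comparators {6b}, Limitations | testing | all, whatever the incentive |

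Only the first row makes the payment depend on dispensing.

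**Amount contingent on initiation in PCR-positive participants**

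- Under Table 2 and {18b}: 0, 50, ..., 1,000.
- Under the literal step: 0 + 105 = 105, 50 + 105 = 155, ..., 1,000 + 105 = 1,105.
- Top minus control is 1,000 in both cases. The gaps between arms are unchanged and only the starting point moves.

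**Illustration of size.** The article gives no figure that depends on this point, so there is nothing to reproduce. Inputs from Sample size {14}: baseline about 15%, and +20 points across the range, so 35% at AUD 1,000. The ED50 and Hill values are assumptions. The curve is taken as the response to money contingent on initiation:

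logit p(d) = logit(0.15) + E·f(d), with f(d) = d^h / (ED50^h + d^h) and E = [logit(0.35) − logit(0.15)] / f(1000) = 1.1156 / f(1000).

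Worked case, ED50 100 and h = 2:

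- f(1000) = 0.9901, so E = 1.1156/0.9901 = 1.1267.
- f(105) = 11,025/21,025 = 0.5244. logit p(105) = −1.7346 + 1.1267 × 0.5244 = −1.1438, so p(105) = 24.2%, a rise of 9.2 points.
- f(1105) = 0.9919, so p(1105) = 35.0%. Top contrast p(1105) − p(105) = 10.9 points.

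| ED50, Hill | Rise in control, p(105) − p(0) | Top contrast, p(1105) − p(105) (20.0 without shift) | Nominal dose giving +10 points: without shift → with shift |
|---|---|---|---|
| 100, 2 | 9.2 | 10.9 | 114 → 368 |
| 200, 1 | 6.9 | 13.5 | 181 → 430 |
| 500, 1.2 | 2.9 | 18.0 | 353 → 381 |
| 400, 4 | 0.1 | 20.1 | 423 → 319 |

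An earlier rise makes it worse. With ED50 50 and Hill 1, the control response is 28.1%, the top contrast is 7.0 points, and no dose reaches +10. A late, steep rise leaves the top contrast almost untouched and lowers the nominal dose needed.

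**The case against.** The strongest reply is that the sentence is loose, not wrong. It names two proofs and two payments. Taken respectively (the test releases the compensation, the dispensed DAA releases the incentive), it agrees with Table 2 and {18b}. Table 1 lists PCR confirmation as its own event. The reminder to a tested participant without a filled prescription mentions only the incentive as still to be earned. No section says that a PCR-positive non-initiator is refused payment, and the full protocol is not shown. This reading is possible, so the fault may lie in the wording and not in practice. But the sentence does not say it, the follow-up section fits joint payment, and the negative-result sentence shows that a test-only trigger could be written plainly.

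A second reply is that {6b} and the Limitations already disclose compensation in all arms. They do, but as payment for testing. That does not cover a payment that depends on the primary endpoint.

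Three stronger readings are tempting and not supported:

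- *The randomised comparisons are biased.* The AUD 105 is the same in every arm, so contrasts are not confounded. What changes is the meaning of AUD 0 and the position on the curve.
- *The minimum effective dose is understated.* The direction depends on the curve. In the table the dose rises in three cases and falls in one.
- *Participants already randomised need a separate analysis period.* That presumes that navigators withheld the payment and that practice will change. Nothing in the article shows either.

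On the secondary endpoint, participants are expected to report results whether positive or negative, and navigators follow up. Under-recording is therefore possible, not established.

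**Conclusion.** The inconsistency is real. For PCR-positive participants, the literal payment step conflicts with Table 2, {6b}, {18b} and the Limitations, and leaves the payment of PCR-positive non-initiators unstated. If it is followed, every arm carries a further AUD 105 contingent on initiation, and AUD 0 is no longer an arm without an incentive.

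The size is conditional on two things. The first is that navigators apply the joint trigger, which the article does not establish. A reader might infer that the control arm is in fact an AUD 105 arm, but the text supports only that it would be one if the step were followed. The second is the curve shape. Over the four assumed shapes, the control response rises by 0.1 to 9.2 points, the top contrast becomes 10.9 to 20.1 points against a 10-point criterion, and the dose needed moves either way. The illustration also treats the planned 15% as the response with nothing contingent on initiation. The article does not say whether that figure already allows for the compensation. If it does, adding 105 counts it twice.

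**What to change.** 1. Reword the payment step, and the follow-up section with it, to agree with Table 2, {6b}, {18b} and the Limitations. Evidence of the PCR test releases the AUD 105, whatever the result and independent of dispensing. Dispensing releases only the randomised incentive and any prescriber payment. State when a PCR-positive participant who does not start DAA is paid.
2. Document which rule navigators have applied and from what date. Recruitment was under way, with 186 randomised when the article was submitted.
3. Only if the joint trigger was in fact used, say so when interpreting AUD 0 and reflect it in the economic analysis.

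The cost is a change of wording and of navigator instructions, plus AUD 105 for each PCR-positive non-initiator who would otherwise not be paid. The article gives no count of these. As an assumed example, 100 such people would cost 100 × 105 = AUD 10,500. Compensation comes from the same fixed funds as the incentives, so this leaves slightly less for incentives.

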#### Follow-up

Following confirmation that DAA has been dispensed, the participant is informed that they will be contacted in:(i)2–4 weeks following treatment initiation to confirm their receipt of the compensation + / − incentive payment and to document any untoward health-related events, and(ii)4–5 weeks after the expected date of completion of DAA therapy to facilitate a follow-up appointment with their treatment prescriber to test for a viral response (negative HCV PCR at least 28 days after completing therapy). At this end of treatment follow-up, the navigator also confirms and documents the participant’s self-reported adherence to treatment (recalled number of missed days of medication).

#### Evidence of SVR

The navigator organises a final follow-up call to sight and verify the participant’s end-of-therapy HCV PCR results, following which the participant receives AUD 75 as an HCV test compensation payment via digital or physical gift card. This payment is provided whether a viral response has been achieved or not, and this completes the study for the participant.

#### Discontinuation/withdrawal of participants

Enrolled participants may withdraw from the study at any time and consent may be reassessed by the navigator across the duration of the study to ensure it is accurate and up to date. Consent for any data collected to be used for future research purposes may also be invoked or withdrawn by the participant at any time.

### Sample size {14}

The intervention is the offer of a financial incentive at registration, which may subsequently become an actual payment upon evidence of initiating DAA therapy. Consequently, the sample size will be constrained by the realised dose–response curve and the fixed project budget awarded by the funding body. For example, if the dose–response moves from its lowest to highest response (treatment initiation) at relatively low value incentives, then the randomisation mechanism will lead to participants being preferentially allocated to lower value incentives allowing for more participants to be enrolled than when higher incentive values are required to motivate treatment initiation.

Through simulation over a range of scenarios, the expected total sample size ranged from 580 to 2000, dependent on the specific form of the dose response considered. In the null case, that is where there was no increase in the DAA initiation over the entire dose–response range, the study was suspended for futility in all simulated trials with an expected sample size of 580 enrolled participants. Across all scenarios, the type-I error was maintained below 6%. Non-null scenarios focused on a baseline response of approximately 15% and an increment of 20 percentage points (in absolute terms) across the incentive range. Depending on the shape of the dose–response curve, the probability of identifying an effective dose ranged from 80 to 99%.

